## Background

Acute coronary syndrome (ACS) is a leading cause of death and hospitalization in developed countries. In recent decades, the mortality and morbidities after ACS have been remarkably decreased with improvement in percutaneous coronary intervention (PCI) with a drug-eluting stent (DES) and treatment with antiplatelet agents [1, 2].

Prasugrel is a novel thienopyridine that irreversibly binds to the platelet P2Y12 receptor and inhibits adenosine diphosphate-induced platelet aggregation. Both agents are thienopyridine P2Y12 inhibitors, but prasugrel is more potent and has less variability in platelet inhibition than clopidogrel. In the TRITON-TIMI 38 trial enrolling ACS patients with planned PCI (mostly after diagnostic angiography), prasugrel significantly reduced ischemic events including stent thrombosis (ST) but increased major bleeding episodes, including fatal ones, compared with clopidogrel [3]. Currently, guidelines recommend prasugrel as an initial P2Y12 inhibitor over clopidogrel, unless the patients are older than 75 years of age, have low body weight (<60 kg), or previous history of transient ischemic attack or stroke [4]. Nonetheless, clinical efficacy and safety of prasugrel in Asians are still unclear. Studies have shown marked inter-ethnic difference in the pharmacokinetics and pharmacodynamics of prasugrel. Asians showed higher serum prasugrel levels with greater platelet inhibition than Caucasians at the same dose of prasugrel [5]. In terms of balance between bleeding and thrombosis, Asians have a lower risk of thrombotic event while a higher risk of bleeding in previous studies [6]. In addition, East Asians have not been properly enrolled in major clinical trials with prasugrel (7.8 % in TRIOLGY ACS, and 0.9 % in TRITON-TIMI 38) [3, 7]. In this regard, concerns need to be addressed in a dedicated trial of East Asians as to whether the currently recommended dose of prasugrel (60 mg loading/10 mg daily maintenance) is efficacious and also safe in East Asians.

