### Outcome measurements and definitions

There are two primary endpoints in this study. In the stent comparison arm, the primary endpoint will be POCO, defined as a composite of all-cause death, nonfatal MI, and any repeat revascularization at 12 months. In the prasugrel dose comparison arm, the primary endpoint will be MACE, defined as a composite of all-cause death, nonfatal MI, ST, repeat revascularization, CVA, and BARC class ≥ 2 bleeding at 12 months. Revascularization is considered clinically driven with follow-up angiographic diameter stenosis ≥ 50 %, and at least one of the following: 1) history of recurrent angina pectoris, presumably related to the target vessel; 2) objective signs of ischemia at rest or during exercise testing (or equivalent), presumably related to the target vessel; 3) abnormal invasive functional diagnostic testing; or 4) target lesion or target vessel revascularization with ≥ 70 % diameter stenosis, even without aforementioned ischemic signs/symptoms [24, 25]. To reduce the chance of so-called “oculostenotic reflex,” whereby rates of repeated revascularization are disproportionately high, investigators will be recommended to perform a non-invasive stress test prior to the decision of the re-intervention of the target lesions as much as possible and they will adhere strictly to a clinically driven revascularization protocol. All clinical outcomes were defined according to the Academic Research Consortium (ARC) [25, 26]. All clinical events including revascularization will be independently adjudicated by an independent event adjudication committee, and only clinically driven revascularization will be coded as an event.

Secondary endpoints will be the individual components of the primary endpoints. In addition, POCO and MACE rate at 36 months, device-oriented composite endpoint (composite of cardiac death, target vessel MI, or target lesion revascularization), and acute procedure success (device, lesion and procedure) will be included as secondary endpoints. In prasugrel the comparison arm, adherence to the study dose of prasugrel, PRU value by VerifyNow P2Y12 at 1 month, 12 months, and the ratio of patients with the therapeutic range of P2Y12 reaction units (PRU, 86-238) will also be analyzed [27].

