Patients who undergo VerifyNow P2Y12 assay will be also analyzed as a prespecified subgroup analysis. The PRU value will be analyzed using the *t* test n the conventional dose group versus reduced maintain dose group. The ratio of patients with a therapeutic PRU range (86–238 PRU) will be analyzed using the *χ*^2^-test.

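### Neither planned PRU test estimates how many patients in each dose group fall above 238 or below 86, so a higher in-range share at 5 mg could coexist with an unreported rise above 238

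*Protocol article*

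**What the plan says.** The protocol article plans two PRU comparisons between the dose groups.

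- **Endpoints.** Outcome measurements and definitions lists both as secondary endpoints of the prasugrel comparison: "PRU value by VerifyNow P2Y12 at 1 month, 12 months, and the ratio of patients with the therapeutic range of P2Y12 reaction units", with the window set at 86 to 238.
- **PRU value.** Under Statistical analyses, "The PRU value will be analyzed using the" t test, for "the conventional dose group versus reduced maintain dose group".
- **In-range share.** The next sentence reads "The ratio of patients with a therapeutic PRU range (86–238 PRU) will be analyzed using the *χ*^2^-test".
- **Who is analysed.** "Patients who undergo VerifyNow P2Y12 assay will be also analyzed as a prespecified subgroup analysis". The number of such patients is not given.
- **Timing.** Under Study design, the assay is done at the index procedure, 1 month and 12 months. Under Interventions with study device and drug, everyone in the prasugrel comparison takes 10 mg until the 1-month visit.
- **Premise.** The Background states that "Asians showed higher serum prasugrel levels with greater platelet inhibition than Caucasians at the same dose of prasugrel".

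The article neither says that the two out-of-range groups will be separated nor that they will be reported only together.

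**The concern.** PRU measures on-treatment platelet reactivity, so a value below 86 and a value above 238 are opposite failures: inhibition is stronger than the window in the first case and weaker in the second. The chi-square on the in-range share counts both as the same outcome.

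This matters here because the intervention is a dose reduction. The Discussion (Prasugrel dose after PCI) gives the trial two aims, to keep the antiplatelet effect and to limit bleeding. In pharmacodynamic terms these correspond to the two tails. Lowering the dose should move patients along exactly this axis, so a fall below 86 and a rise above 238 can occur together. When the fall is the larger, the in-range share improves and the rise is not visible in it. A higher mean PRU at half the dose is the expected result, and it does not say how many patients crossed 238.

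At stake is how the PRU results are read in support of the reduced dose. The primary endpoints, margins, alpha and sample size are not touched.

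**Working it through.** The document gives no PRU mean, SD, expected in-range share, assay-set size or power, so there is no stated figure to reproduce. The check is an illustration.

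**Inputs.** From the document: the cut-offs 86 and 238, the chi-square on the in-range share, and the t test on the PRU value. Assumed: normal PRU, the means and SDs below, and 50 to 200 assayed patients per group.

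**Formulas.** With Φ the standard normal distribution function:
- share below 86 = Φ((86 − mean)/SD)
- share above 238 = 1 − Φ((238 − mean)/SD)
- in range = 1 − both
- approximate power of the t test, two-sided 0.05 = Φ(gap/(SD·√(2/n)) − 1.96), with n per group

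**Step 1. Can the in-range share alone hide direction?** Yes. Take SD 60 and means placed symmetrically about 162, the midpoint of 86 and 238.

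| Group (assumed mean) | Below 86 | 86–238 | Above 238 |
|---|---|---|---|
| 10 mg (142) | 17.5 % | 77.0 % | 5.5 % |
| 5 mg (182) | 5.5 % | 77.0 % | 17.5 % |

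The in-range shares are equal, so the chi-square has nothing to detect.

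**Step 2. Does the t test reveal this pattern?** Yes. The gap is 40 PRU. With n = 50 per group, 60·√(2/50) = 12, 40/12 = 3.33 and Φ(3.33 − 1.96) = 0.915. With n = 100 power is 0.997. Across SD 50 to 80 it is 0.979 to 0.705 at 50 per group and at least 0.94 at 100. A 20-PRU gap is harder to see: 0.52 to 0.24 at 50 per group and 0.98 to 0.71 at 200.

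**Step 3. What do both tests together leave out?** Take means of 90 (10 mg) and 150 (5 mg), SD 60.
- 10 mg: below 86, Φ(−0.067) = 47.3 %; above 238, 1 − Φ(2.467) = 0.7 %; in range, 52.0 %.
- 5 mg: below 86, Φ(−1.067) = 14.3 %; above 238, 1 − Φ(1.467) = 7.1 %; in range, 78.6 %.

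The chi-square favours 5 mg (+26.6 points in range). The t test shows the expected higher mean (60/12 = 5, Φ(5 − 1.96) = 0.999 at 50 per group). Neither gives an estimate or interval for the rise above 238, from 0.7 % to 7.1 %, about 6.4 points. With the same means that rise is 0.2 % to 3.9 % at SD 50 and 1.7 % to 10.4 % at SD 70.

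**Step 4. Can the mean stand in for the tail?** No. With a 5 mg mean held at 150, the share above 238 is 1.4 % at SD 40, 7.1 % at SD 60 and 13.6 % at SD 80. The same mean is compatible with very different tails.

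**Step 5. Which assay matters?** Both groups take 10 mg up to the 1-month visit, so the 12-month assay is the one at which they have been on different doses.

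**The case against.** The strongest reply is that the in-range test does not stand alone. The sentence before it compares the PRU value by t test, and the two measures are listed side by side as secondary endpoints. A reader might infer that 5 mg and 10 mg could look identical while failing in opposite directions, or that the plan has no power against such a shift. The document does not support that: step 2 shows that a material shift in opposite directions separates the means, and the t test gives the direction. Exactly equal in-range shares also need means that mirror each other about 162, and nothing in the article suggests such symmetry. This part of the reply stands in full.

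The reply also notes that the dose question is decided on MACE, with ischaemic and bleeding components analysed separately as secondary endpoints, and that nowhere does the article say a null in-range test will be read as equal adequacy of inhibition. That is correct and limits the weight of the point.

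Finally, a table of both tails can be called detail for the analysis plan. This stands only in part. The article does not leave the analysis open; it names the cut-offs, the dichotomy and the test. Nothing in it forbids tabulating the tails, but nothing planned estimates them either.

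**Conclusion.** The point holds in a limited form and is minor. The in-range chi-square merges opposite failures. The t test supplies the direction of a mean shift but not the share in either tail, so an improved in-range share at 5 mg could sit beside a rise above 238 that no planned analysis estimates. Under the assumed means of 90 and 150 that rise is 3.8 points at SD 50 (3.92 − 0.15), 6.4 at SD 60 and 8.7 at SD 70 (10.44 − 1.72). These sizes rest entirely on assumed normal distributions and assumed means and SDs; they show that the pattern is possible, not that it is likely. The consequence is confined to the interpretation of one secondary pharmacodynamic endpoint in patients with an assay.

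**What to change.** At 12 months, report the three categories (below 86, 86–238, above 238) by dose group. Give the between-group difference with a 95 % CI separately for PRU above 238 and PRU below 86. Keep the planned in-range proportion and the t test.

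The cost is a sentence of analysis wording: same samples, same assay, same cut-offs. The downside is two extra proportions without multiplicity control, which should be labelled descriptive.

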#### Treatment of missing values

The primary analysis of the study endpoints will not be covariate-adjusted. No imputation methods will be used to infer missing values of baseline variables. For the study endpoints, patients lost to follow-up and subsequently lost to assessment of primary endpoint, will be considered to be censored in the estimation of Kaplan-Meier event rates. As a secondary analysis, we will also examine the patients who have been lost to follow-up. We will perform a comparison of baseline characteristics in patients with versus patients without 1-year follow-up. In addition, a sensitivity analysis will be performed to assess the impact of these patients on the study outcomes.

### Study organization and ethical consideration

The principal investigator, the study coordinator, and the Clinical Trials Center at Seoul National University Hospital (executive committee) are jointly responsible for all aspects of the study protocol and amendments. Site monitoring and data collection will be performed by a dedicated affiliated research coordinator. At appropriate intervals, designated trial monitors will review all investigational data for accuracy and completeness, ensuring protocol compliance. In addition to the Executive Committee, the Steering Committee, Data Safety and Monitoring Board, and the Clinical Event Adjudication Committee will be involved for the duration of the trial. This study was approved by the Institutional Review Board at Seoul National University Hospital (D-1404-142-576), Ulsan University Hospital, Wonkwang University Hospital, Chungbuk National University, Presbyterian Medical Center, and Kangnam Sacred Heart Hospital of Hallym University Medical Center, St. Paul’s Hospital, Yeungnam University Medical Center, Boramae Medical Center, Dongsan Medical Center, Soon Chun Hyang University Hospital Cheonan, Hanyang University Medical Center, Korea University Guro Hospital, Seoul Medical Center, Inje University Ilsan Paik Hospital, Dong-A University Hospital, Seoul National University Bundang Hospital, and Pusan National University Hospital. The protocol of the trial has been registered at http://register.clinicaltrials.gov (NCT02193971).

## Discussion

### Prasugrel dose after PCI

The antiplatelet agent is an important component of successful outcome after PCI. Prasugrel is a novel thienopyridine that irreversibly binds to the platelet P2Y12 receptor. It has faster acting, greater antiplatelet efficacy and more predictable effect than clopidogrel. The TRITON-TIMI 38 trial enrolled ACS patients with planned PCI and showed reduced recurrent cardiovascular events in the prasugrel group, compared with clopidogrel (from 11.2 % to 9.3 %, relative risk reduction 0.82, 9 % confidence interval (CI) 0.73–0.93, *p* = 0.002), mostly driven by a significantly lower risk of MI (from 9.2 % to 7.1 %, relative risk reduction 23.9 %, 95 % CI 12.7–33.7; *p* < 0.001). However, the rates of severe bleeding complications were higher in the prasugrel than the clopidogrel group (hazard ratio (HR) 1.32, 9 % CI 1.03–1.68, *p* = 0.03), driven mostly by an increased risk of spontaneous bleeding as well as fatal bleeding. Currently, ESC/EACTS guidelines recommend prasugrel as an initial P2Y12 inhibitor over clopidogrel, unless the patients are ≥ 75 years of age, with low body weight (<60 kg), or previous history of transient ischemic attack or stroke [4]. Nonetheless, the results from the RCT might not be representing daily real-world practice, especially within the specific populations: for example, the Asian population [30]. Actually, East Asians have not been properly enrolled in any major clinical trials with prasugrel [3, 7]. In addition, there has been much evidence demonstrating the significantly different pharmacokinetics and pharmacodynamics of prasugrel in the Asian population compared with the Western population [5, 6]. In that regard, there are concerns about universal application of the currently recommended dose of prasugrel (60 mg loading/10 mg daily maintenance) to the East Asian population.

In this study, we will compare the two different prasugrel maintenance regimens in Asian patients with ACS undergoing PCI. Patients will be randomized to 2 maintenance dosage regimens: 10 mg daily versus 5 mg daily. All of the enrolled patients will receive the currently recommended loading dose of prasugrel (60 mg), and maintain a 10-mg daily dose for 1 month. After 1-month clinical follow-up, patients will receive a maintenance dosage (10 mg versus 5 mg). Therefore, the HOST-REDUCE-POLYTECH-ACS trial will also provide valuable insight regarding the optimal maintenance dose of prasugrel to guarantee its potent antiplatelet effect as well as to minimize the potential hazard of bleeding complications in the Asian population. In the recent DAPT trial, change of prasugrel to clopidogrel at 30 months after PCI showed a mild increase of clinical events in the short- term period [31]. This cohort will be followed up for 3 years. Thus, we could also evaluate the rebound phenomenon beyond 1 year after change of prasugrel to clopidogrel in Asian people.

### Polymer issue in ACS patients: biostable-polymer PtCr-EES versus BP-BES

There has been concern that DES may increase the risk of ST, especially in the treatment of ACS patients. The main cause of this issue is the polymer, a key component of DES, because it may induce chronic inflammation in the stented artery, leading to thrombosis and restenosis especially in the ACS situation. With evolving technology, contemporary DES with thinner strut and biocompatible polymer consistently showed better efficacy and safety than previous first-generation DES [13–15]. Most of the evidence regarding second- generation DES with biostable polymer were generated from CoCr-EES. However, the newest metal, platinum-chromium alloy, is known as a very inert alloy, and may result in less vessel injury and inflammation after PCI, and emerges as a newer DES platform. Promus Premier^TM^ (Boston Scientific Korea, Seoul, Korea) is platinum-chromium-based everolimus-eluting stent, which adopted polyvinylidene fluoride-co-hexafluropropylene (PDVF-HFP) biocompatible polymer. The PDVF-HFP mimics the phospholipids on the outside of red blood cells and enables the polymer to induce minimal thrombus formation. These enhanced technologies might show at least non-inferior efficacy and safety, compared with third-generation BP-BES.

For the counterpart of the stent comparison arm, BP-BES adopted PDLLA which is fully metabolized within 6–9 months in the human body, for reducing inflammation and risk of ST. In the LEADERS trial, BP-BES was shown to be associated with a significant reduction in very late ST (5-year relative risk reduction 74 %, *p* = 0.003) and composite clinical outcomes compared to durable-polymer sirolimus-eluting stent [16]. In addition, BP-BES has shown better efficacy and a better safety trend than BMS in the COMFORTABLE AMI trial [32]. The pooled analysis of individual patient data from the ISAR-TEST 3, ISAR-TEST 4, and LEADERS trial also showed significantly reduced rates of ST with BP-BES, compared with the durable polymer sirolimus-eluting stent (HR 0.56, 95 % CI 0.35–0.95, *p* = 0.015), mainly driven by lower rates of very late ST (HR 0.22, 95 % CI 0.08–0.61, *p* = 0.004) [33].

Although biodegradable polymer technology has been highlighted as a new paradigm in developing DES, concerns are still present. Some studies revealed that BP-BES was also associated with inflammation and a cytotoxic effect as with other DES before polymer degradation [34, 35]. In addition, although recent head-to-head comparison between BP-BES with CoCr-EES showed comparable clinical outcomes up to 2 years of follow-up (NEXT trial) or up to 3 years of follow-up (COMPARE II trial), the COMPARE II trials showed a trend showing higher risk of ST in BP-BES than EES [18–20]. Moreover, currently available network meta-analysis consistently showed superior efficacy and safety of CoCr-EES, even to BP-BES. However, there are some controversies surrounding these network meta-analysis results. The included trials of the BP-BES group which showed significant diversity with the use of 17 different platforms of BP-BES: for example, Biomatrix®, Nobori®, Coracto, EucaTax, EXCEL, Yukon Choic PC, Jactax, Firehawk, SYNERGY, etc. [21]. Furthermore, meta-analyses have adopted clinical results at short-term follow-up as 1 year when polymer has not yet completely gone on BP-BES. Thus, controversies may originate from paucity of data regarding head-to-head comparison between BP-BES directly with second- generation DES for sufficient duration. In addition, the efficacy and safety of the BP-BES have not been compared directly with the second-generation biostable-polymer DES in the ACS situation where the polymer issue may be more critical. This cohort will be followed up for 3 years. Thus, we could evaluate the clinical outcome in the chronic phase when polymer has complete gone on BP-BES while remaining on PtCr-EES. Therefore, the trial will clarify the comparison of clinical outcomes between biostable polymer PtCr-EES and BP-BES and will provide valuable evidence regarding the optimal treatment strategy for the ACS patients.

After initiation of the ‘Harmonizing Optimal Strategy for Treatment of coronary artery diseases – comparison of REDUCtion of prasugrEl dose or POLYmer TECHnology in ACS patients’ (HOST-REDUCE-POLYTECH-ACS) trial, patient enrollment will be done within 2 years. This large and well-designed randomized controlled study will provide insights inton the two critical issues in PCI for ACS patients. First, it will answer the question regarding the optimal maintenance dose of prasugrel beyond 1 month after PCI by comparing 5 mg versus 10 mg of prasugrel in Asian ACS patients. Second, it will clarify the implication of the polymer issue in ACS patients by showing clinical outcomes of biostable polymer PtCr-EES versus BP-BES in real-world practice.

## Trial status

The HOST-REDUCE-POLYTECH-ACS randomized controlled clinical study with a 2 × 2 factorial design is currently ongoing. Patient recruitment was started in October, 2014 and follow-up is being conducted.

### Limitations

The possible expected limitations of the current trial should be acknowledged. Firstly, we set the statistical power of the prasugrel arm as 75 %. About 30 % of the stent comparison arm would not be enrolled in the prasugrel arm due to several factors (absolute or relative contraindication of prasugrel use, or other clinical circumstances including high risk of bleeding); therefore, sample size of prasugrel arm will be inevitably lower than stent comparison arm. With the limited sample size of the stent comparison arm, it was considered to be difficult to further enhance statistical power of the prasugrel arm in contemporary practice in Korea.

## Abbreviations

ACS: acute coronary syndrome
ARC: Academic Research Consortium
BARC: Bleeding Academic Research Consortium
BES: biolimus-eluting stent
BMS: bare metal stents
CAG: coronary angiography
CI: confidence interval
CoCr-EES: cobalt-chromium-based EES
CVA: cerebrovascular accident
BARC: Bleeding Academic Research Consortium
DES: drug-eluting stent
EES: everolimus-eluting stent
IFU: instructions for use
HR: hazard ratio
MACE: major adverse clinical events
MI: myocardial infarction
PCI: percutaneous coronary intervention
PDLLA: poly-D-L-lactic acid polymer
POCO: patient-oriented composite outcomes
PDVF-HFP: polyvinylidene fluoride-co-hexafluropropylene
PRU: P2Y12 Reaction Units
PRU P2Y12 Reaction Units PtCr-EES: platinum-chromium-based EES
ST: stent thrombosis
STEMI: ST-segment elevation myocardial infarction
